### Liquid chromatography - tandem mass spectrometry (LC-MS/MS)

2.7

LC-MS/MS analysis will be performed using a Vanquish UHPLC system (Thermo Fisher) coupled with an Orbitrap Q Exactive HF-X mass spectrometer (Thermo Fisher) operating in the data-dependent acquisition (DDA) mode. Samples (dialysate) were injected onto an Accucore HILIC column (100 × 2.1 mm, 2.6 μm) using a 20-minute linear gradient at a flow rate of 0.3 mL/minute. The eluents of the positive polarity mode were eluent A (0.1% FA in 95% ACN, 10 mM ammonium acetate) and eluent B (0.1% FA in 95% ACN, 10 mM ammonium acetate). The eluents of the negative polarity mode were eluent A (95% ACN, 10 mM ammonium acetate, pH 9.0) and eluent B (50% ACN, 10 mM ammonium acetate, pH 9.0). The solvent gradient was set as follows: 2% B, 1 minute; 2% to 50% B, 16.5 minutes; 50% to 2% B, 2.5 minutes. Q-Exactive HF-X mass spectrometer was operated in positive/negative polarity mode with spray voltage of 3.2 kV, capillary temperature of 320°C, sheath gas flow rate of 35 arb and aux gas flow rate of 10 arb.

In order to detect metabolites, we will carry on the principal component (PCA) and orthogonal partial least-squares (OPLS-DA) analysis. Through MzCloud database the potential differences metabolites will be identified, then use Kyoto encyclopedia (KEGG) gene and genome data analyze the related metabolic pathways.

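### As written, positive-mode eluents A and B are the same solvent, which contradicts the stated 2% to 50% B gradient; eluent B is probably misprinted and needs to be stated correctly

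*Protocol article*

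**What the plan says.** All the relevant text on the chromatography is in section 2.7 (LC-MS/MS) of the protocol article.

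- **Column:** "Accucore HILIC column (100 × 2.1 mm, 2.6 μm").
- **Elution:** "using a 20-minute linear gradient at a flow rate of 0.3 mL/minute".
- **Positive-mode solvents:** "eluent A (0.1% FA in 95% ACN, 10 mM ammonium acetate) and eluent B (0.1% FA in 95% ACN, 10 mM ammonium acetate").
- **Negative-mode solvents:** "eluent A (95% ACN, 10 mM ammonium acetate, pH 9.0) and eluent B (50% ACN, 10 mM ammonium acetate, pH 9.0").
- **Programme:** "2% B, 1 minute; 2% to 50% B, 16.5 minutes; 50% to 2% B, 2.5 minutes". It is given once and is not split by polarity.
- **Acquisition:** the mass spectrometer is "operated in positive/negative polarity mode".

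Section 2.9 makes the metabolites found to differ between patients and volunteers the primary outcome. LC-MS/MS is the only assay the article describes for finding them. No other part of the article gives a different positive-mode composition.

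**The concern.** A gradient needs two solvents that differ. In positive mode the acetonitrile, formic acid and ammonium acetate contents of A and B are all the same, so changing the proportion of B cannot change the mobile phase. The positive-mode recipe and the stated gradient cannot both be right.

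The point deserves attention because of where it sits. It is a stated operating parameter of the assay that produces the primary outcome. On a HILIC column, as a matter of general chromatography, a rising water fraction is what drives polar compounds off the column. If water stayed at about 5% for the whole run, strongly polar metabolites could be held back or broadened, and some might not be detected. The introduction mentions histamine, serotonin and adenosine as substances already linked to acupoints; these illustrate the kind of small polar molecule involved, although the article does not name them as targets of this study. At the least, a reader could not reproduce the positive-mode method from the text.

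**Working it through.** **Inputs (section 2.7).** Acetonitrile (ACN) in positive mode: A 95%, B 95%. In negative mode: A 95%, B 50%. Fraction of B, written f: 0.02 at the start of the ramp and 0.50 at its end. Segments: 1, 16.5 and 2.5 minutes.

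**1. Reproduce the stated run length.** 1 + 16.5 + 2.5 = 20 minutes. This agrees with the article, so the programme is consistent in time.

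**2. Acetonitrile in the mixed mobile phase.** ACN(f) = ACN_A × (1 − f) + ACN_B × f.

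| Mode, as written | f = 0.02 | f = 0.50 | Change |
|---|---|---|---|
| Positive | 95 × 0.98 + 95 × 0.02 = 95.0% | 95 × 0.50 + 95 × 0.50 = 95.0% | 0.0 points |
| Negative | 95 × 0.98 + 50 × 0.02 = 94.1% | 95 × 0.50 + 50 × 0.50 = 72.5% | 21.6 points |

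The negative-mode slope is 21.6 / 16.5 = 1.31 points per minute. Ignoring the small volume of additives, water rises from 5.9% to 27.5% in negative mode and stays at 5% in positive mode. Formic acid and ammonium acetate are also equal in positive-mode A and B, so no other component supplies a gradient.

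**3. What a corrected eluent B would give.** The article does not state the right value, so this is an assumption with a range.

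| Assumed ACN in positive-mode B | Start of ramp | End of ramp |
|---|---|---|
| 40% | 93.9% | 67.5% |
| 50% (as in negative mode) | 94.1% | 72.5% |
| 60% | 94.3% | 77.5% |

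Any of these restores a real gradient. The arithmetic cannot show which one the laboratory uses.

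**4. Material available for a repeat.** The Discussion gives 0.3 µl/minute for exchange at the probe. Taking this as the perfusion rate (an assumption), each 60-minute collection in section 2.5 yields 0.3 × 60 = 18 µl, and the three collections of a visit yield 54 µl. The Discussion cites an LC-MS/MS method with a starting volume of 25 µl. If this assay needed about that much per analysis (also an assumption), 54 / 25 = 2.16, or about two analyses from the pooled dialysate of one visit. If each polarity mode used one such portion, the two modes would take 50 µl and leave about 4 µl. If one portion served both modes, 29 µl would remain.

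**The case against.** The strongest reply is that this is a slip in a condensed article and not a plan to run the assay without a gradient. The same section calls the elution a linear gradient, names two separate eluents, programmes their mixing, and prints a negative-mode pair that differs as expected. A laboratory has little reason to prepare two bottles of one solvent and mix them. Bench compositions are normally governed by an operating procedure that is not shown here. The slip changes no sample size, comparison, outcome definition or analysis step, and section 2.1 describes the study as an exploratory pilot.

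Most of this stands. Four stronger readings that a reader might infer are not supported:

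- **That positive mode is in fact run isocratically.** The article shows only that the recipe as written would be isocratic.
- **That half of the metabolomics data is lost.** One of two polarity modes is affected. The article gives no share of metabolites per mode.
- **That metabolites will be missed and carry-over will add noise.** These harms depend on the recipe being followed literally, and the article has no figure for either.
- **That the group comparison is biased.** Both groups are to be assayed by the same method, so reduced coverage would not by itself favour either one.

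The reply does not remove the contradiction. The composition is stated, and stated inconsistently, so this is not a detail left to a fuller document. It sits in running prose beside an intact negative-mode description, which makes a PDF-reading fault unlikely.

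**Conclusion.** The concern holds as an internal contradiction in a stated assay parameter. As written, positive-mode acetonitrile changes by 0.0 points over the ramp, against 21.6 points in negative mode, and nothing else in the article corrects this. That conclusion rests only on the stated compositions and programme.

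The practical consequence is conditional. If eluent B is merely misprinted, the effect is limited to the reproducibility of the published method. If the recipe were followed, one of the two polarity modes of the primary-outcome assay would have no gradient, with possible loss of separation and detection for strongly polar metabolites. The article cannot tell us which case applies, although a misprint is the more likely. The sponsor can settle it by consulting the laboratory procedure.

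**What to change.** Before any sample is run, check positive-mode eluent B against the laboratory's operating procedure, state its actual composition in section 2.7, and confirm that it is consistent with the 2% to 50% B programme. The negative-mode value of 50% acetonitrile should not be copied across without that check.

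The sponsor should also confirm whether any samples have already been analysed with identical eluents. If so, re-run them in positive mode only where enough dialysate remains. Where it does not, keep the positive-mode results but report that they were obtained without a gradient.

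The cost is one line of text and one query to the laboratory if the right eluent is already in use. A repeat would cost instrument time and dialysate, and may not be possible for every sample. Baseline dialysate from patients cannot be collected again once the 20 treatment sessions have been given, which is the reason to check first.

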### Sample size calculation

2.2

This study aims to investigate basic information about sensitized acupoints of KOA patients, rather than to satisfy hypothesis testing. Hence, the sample size was estimated by based on a rationale about feasibility, precision about the mean and variance, regulatory considerations and ethical issues that prohibit over-recruitment of participants. Considering an estimated 20% dropout rate, we assured that the sample size exceeded the minimal number needed to ensure the validity of the mean, effect size and rationale of feasibility. Therefore, a sample size of 60 participants was estimated.

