### Recruitment KOA patient and healthy volunteers

2.3

A total of 30 KOA patients and 30 normal volunteers will be included, flow diagram in Figure 1. No interim analysis will take place. Subjects enrolled will have some financial compensation, and KOA patients can also receive 4 weeks free electro-acupuncture treatments. And all information about the subject will be kept strictly confidential until the end of the trial.

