### Micro dialysis

2.5

The highest sensitized acupoint of KOA patients and the same acupoint of volunteers will choose for micro dialysis. Disinfect locally with 75% alcohol, cover disposable surgical hole towel. The skin overlying the muscle of the puncture sites will be anesthetized with a local injection (0.5 ml) of Lidocaine (Xylocaine 20 mg /ml), carefully avoiding anaesthetized the underlying muscle.

Insert introducer cannula into muscle tissue below acupoint. Guide the catheter (CMA 66 Liner Catheter, Membrane: PAES, Membrane length 10 mm, Cut-off 20,000 Dalton, Inlet 400 mm, Outlet 100 nm. M dialysis AB, Sweden) gently in to the sharp end of introducer cannula (Important: be very careful when entering membrane into introducer cannula). When catheter and membrane are in position, remove introducer cannula. Penetrate vial cap with a cannula (preferably 21G). Position cannula at the catheter outlet, removes the cannula from outlet, and then connect microvial. Then connect catheter to syringe filled with Perfusion Fluid (CMA, M dialysis AB, Sweden). Place the syringe in the microdialysis pump (CMA 106, M dialysis AB, Sweden). A 5 minutes flush will start indicated by a green signal every other second. Then after 120 minutes of equilibration the dialysate will collect every 60 minutes for a total of 3 collections. The dialysate will store frozen in –80° refrigerator as soon as possible.

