### Intervention method

2.6

After highly sensitized acupoint screening and dialysate sample collecting, 5 to 6 sensitized acupoints will be chose to the main points. Then, KOA patients will receive electro-acupuncture treatment 5 sessions per week for 4 weeks, with continuous wave and durations of 30 minutes, the electricity intensity is based on the patient's tolerance. Relevant concomitant care and interventions that are permitted or prohibited during the trial. At the end of the treatment, the sensitized acupoints will be detected again to see whether MPTs had changed, and the previous most sensitized acupoint will be collected dialysate sample again.

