### Outcome measure

2.9

The primary outcome is the identified potential differences metabolites between KOA group and volunteer group will be the outcome measures. And the second outcome is the change of Western Ontarioand McMaster Universities Osteoarthritis Index (WOMAC) total score from baseline to 4 weeks of KOA patients.

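### Section 2.7 names only PCA and OPLS-DA for dialysate that KOA patients give both before and after treatment; the before/after comparison should be made within person

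*Protocol article*

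**What the plan says.** The sampling has two layers within each person.

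- **Across visits.** Section 2.6 returns to the KOA patients at the end of treatment: "the previous most sensitized acupoint will be collected dialysate sample again". The Abstract describes the same sequence of sampling, treating and sampling again, followed by LC-MS/MS.
- **Within a session.** Section 2.5: "after 120 minutes of equilibration the dialysate will collect every 60 minutes for a total of 3 collections".

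For analysis, section 2.7 says "we will carry on the principal component (PCA) and orthogonal partial least-squares (OPLS-DA) analysis", and then moves to metabolite identification and pathway look-up, neither of which is a statistical comparison.

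Section 2.9 defines the outcomes. "The primary outcome is the identified potential differences metabolites between KOA group and volunteer group" is a contrast between persons. The one before/after outcome listed is clinical: "the second outcome is the change of Western Ontarioand McMaster Universities Osteoarthritis Index (WOMAC) total score from baseline to 4 weeks of KOA patients". No listed outcome uses the post-treatment dialysate. The Abstract's conclusion and the Discussion nevertheless treat its purpose as a study aim: whether acupuncture acts through local molecules, and what part those molecules play in treatment.

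**The concern.** OPLS-DA separates classes of rows that it takes as unrelated. Pre- and post-treatment profiles of one patient are related: stable differences between people (age, tissue, catheter site, disease grade) appear in both. If the two visits are simply two classes, those differences stay in the noise against which the change is judged. The error is conservative, and its cost is missed changes. Patients undergo a second catheter session to supply this sample, and it is the only dialysate that can speak to the treatment aim.

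The three fractions raise a separate question that runs the other way. If they were entered as separate rows in the KOA versus volunteer comparison, correlated rows would count as independent people and the result would look stronger than it is.

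**Working it through.** **The plan's own figure.** The total of 60 cannot be reproduced by formula, because section 2.2 gives no alpha, power, effect size or SD. It is consistent with 48 completers, 48 / (1 - 0.20) = 60, but 48 is not stated. Nothing below changes that figure.

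**Inputs from the article.** 30 KOA patients and 30 volunteers (section 2.3); 20% dropout (section 2.2), so 30 x 0.8 = 24 completers per group; three 60-minute fractions per session (section 2.5); flow of 0.3 µl per minute and a cited assay's 25 µl starting volume (Discussion).

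**Assumptions, not in the article.** Within-person correlation r or ICC of 0.3 to 0.7; a true shift d = 0.5 SD; a two-sided 5% test per metabolite with no multiplicity correction. A t test stands in for the comparison, since OPLS-DA has no power formula.

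**Step 1: before/after, n = 30.** The mean change has variance 2(1 - r)/n in SD units.

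- Paired power: Φ(d / √(2(1 - r)/n) - 1.96). At r = 0.5: √(1/30) = 0.183; 0.5 / 0.183 = 2.74; Φ(0.78) = 78%.
- Unpaired test on the same paired data: Φ((d√(n/2) - 1.96) / √(1 - r)). At r = 0.5: (1.936 - 1.96) / 0.707 = -0.03; Φ = 49%.
- True alpha of the unpaired test: 2(1 - Φ(1.96 / √(1 - r))).

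The simulated columns use t tests with 20,000 replicates.

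| r | Paired, formula | Paired, simulated | Unpaired, formula | Unpaired, simulated | True alpha, unpaired |
|---|---|---|---|---|---|
| 0.3 | 64% | 61% | 49% | 48% | 1.9% |
| 0.5 | 78% | 75% | 49% | 46% | 0.6% |
| 0.7 | 94% | 93% | 48% | 47% | 0.03% |

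With 24 completers and r = 0.5, the formulas give 69% paired against 37% unpaired, and simulation gives 65% against 36%. At r = 0 both formulas reduce to Φ(-0.02) = 49%, so the whole gain comes from the correlation.

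**Step 2: are the fractions pooled?** One fraction is 0.3 x 60 = 18 µl; three are 0.3 x 180 = 54 µl. A single fraction falls short of 25 µl, and the three together exceed it. That leans towards pooling. It does not prove it, because 25 µl describes a cited method and is not given as this trial's volume.

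**Step 3: only if the fractions are separate rows.** There would be 30 x 3 = 90 rows per group. Design effect = 1 + (3 - 1) x ICC; true alpha = 2(1 - Φ(1.96 / √DE)).

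| ICC | Design effect | Effective rows per group | True alpha |
|---|---|---|---|
| 0.3 | 1.6 | 56 | 12% |
| 0.5 | 2.0 | 45 | 17% |
| 0.7 | 2.4 | 38 | 21% |

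Simulated t tests agree, and one mean per person restores about 5%. Cross-validation would not expose the problem if folds split a person's fractions. With 500 pure-noise features, two components and seven folds, null Q2 averages 0.41, 0.65 and 0.79 at ICC 0.3, 0.5 and 0.7. Whole-person folds give -0.26 to -0.15.

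**The case against.** The strongest reply is that the article does not commit to either faulty analysis. Section 2.9 lists no before/after metabolite outcome, section 2.7 does not say that the two visits will be OPLS-DA classes, and pooling rules and cross-validation folds commonly belong to a full protocol or SAP that is not shown. The trial is an exploratory pilot whose size was not set by hypothesis testing, so every power and error rate above describes a test supplied for illustration.

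Much of this stands. A reader might infer that 180 baseline fractions (60 x 3) will be entered as rows and that the primary KOA versus volunteer result will therefore be falsely strong. The documents do not support that: no sentence says so, and the volumes lean the other way. Nor is OPLS-DA unsuitable for the primary contrast as such, since with one profile per person it has the right unit.

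What does not fall is the mismatch over the repeat sample. The article itself fixes the paired collection, states an aim that only this collection can serve, and names a single method that cannot use the pairing. An exploratory purpose does not help: a search for candidate substances gains from power as much as a confirmatory test does.

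**Conclusion.** The point holds for the before/after dialysate. The only method named does not fit paired samples, and using it with visits as classes would give up roughly 13 to 46 percentage points of power (61% against 48% at r = 0.3; 93% against 47% at r = 0.7, both simulated), with about 29 points at r = 0.5 (75% against 46%). These sizes rest on the assumed 0.5 SD shift, 30 pairs and a 5% per-metabolite test. The direction needs only a positive within-person correlation.

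For the three fractions the conclusion is conditional. The inflation to 12-21% arises only if fractions are analysed separately as independent rows; if they are pooled before injection, it disappears and the paired point is unaffected. No error in the primary comparison is shown.

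**What to change.** In section 2.7:

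1. State that the before and after dialysate of KOA patients will be compared within person, by multilevel (within-subject) PLS-DA or by a paired test on each patient's log change per metabolite.
2. State whether the three fractions are pooled. If they are analysed separately, either reduce them to one profile per person per session (for example, the mean log intensity) before PCA and OPLS-DA, or form cross-validation folds and permutations by whole person and use a random person effect in any per-metabolite model.

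The cost is wording: no new patients, visits or samples. The downside is that the primary comparison visibly rests on 60 profiles, so separation may look less striking than with 180 rows, and averaging or pooling gives up fraction-by-fraction detail in that analysis.

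### The primary outcome is a list of metabolites selected from the data; the only group-comparing method named is OPLS-DA, with no validation or error limit stated, and at 30 v 30 that method separates noise

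*Protocol article*

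**What the plan says.** Section 2.9 (Outcome measure) states: "The primary outcome is the identified potential differences metabolites between KOA group and volunteer group". The primary outcome is thus itself the product of a selection step, not a quantity measured on each participant.

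Section 2.7 (LC-MS/MS) gives the route to that list. First, "we will carry on the principal component (PCA) and orthogonal partial least-squares (OPLS-DA) analysis". Then, "Through MzCloud database the potential differences metabolites will be identified", and KEGG is used for the related pathways. MzCloud puts names to features; it does not judge whether a feature differs between groups. PCA ignores group membership. OPLS-DA is therefore the only method named that compares the groups.

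The article gives no importance cut-off, fold change, p-value, multiplicity rule, cross-validation or permutation test. It does not exclude any of them either. The number of features is not stated; the introduction describes the assay as non-targeted.

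**The concern.** OPLS-DA looks for the direction in the data that best reproduces the group labels. When features far outnumber people, such a direction can be found in pure noise, so the fitted model looks convincing on the data that built it whether or not the groups differ. Metabolites picked by their weight in that model inherit the problem.

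Usually an outcome is defined in the protocol and its test is detailed in the analysis plan. Here the outcome is the output of the selection, so without a selection rule it is not fully defined. The only group-comparing tool named cannot, on in-sample fit alone, tell signal from overfitting. At stake is whether the reported key substances and pathways reflect acupoint sensitization or chance. The abstract's Results paragraph claims strong evidence on the local mechanism, so readers are likely to take the list at face value.

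**Working it through.** **Inputs from the article.** Section 2.3: "A total of 30 KOA patients and 30 normal volunteers will be included". Section 2.2: "a sample size of 60 participants was estimated", with the qualifier "Considering an estimated 20% dropout rate". This gives 60 × (1 − 0.20) = 48 completers, or 24 per group; in reverse, 24 / 0.8 = 30 per group. The article states no minimum n, alpha, power, effect or SD, so 60 can be neither derived nor refuted, and nothing below depends on it beyond the group sizes.

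**Assumptions.** 50 to 3000 features; features either independent or driven by 10 latent factors carrying a set share of the variance; unit-variance scaling; one predictive and one orthogonal component; VIP > 1 as the importance cut-off. None of these is in the article.

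**Step 1: separation of noise.** Data were simulated with no group difference at 30 v 30 (100 runs per setting, 40 at 3000 features). Each cell gives independent features / features with a 50% factor share.

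| Features | In-sample accuracy | 7-fold cross-validated accuracy | Cross-validated Q2 |
|---|---|---|---|
| 50 | 0.90 / 0.83 | 0.49 / 0.49 | −0.69 / −0.49 |
| 100 | 0.985 / 0.90 | 0.49 / 0.50 | −0.53 / −0.49 |
| 200 | 1.00 / 0.945 | 0.47 / 0.50 | −0.37 / −0.49 |
| 500 | 1.00 / 0.97 | 0.47 / 0.49 | −0.17 / −0.45 |
| 1000 | 1.00 / 0.98 | 0.47 / 0.48 | −0.10 / −0.45 |
| 3000 | 1.00 / 0.98 | 0.43 / 0.50 | −0.06 / −0.39 |

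Cross-validation on the same data shows that there is nothing to find. At 24 v 24 the in-sample accuracy is 0.86 to 1.00.

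**Step 2: sensitivity to correlation.** In-sample accuracy at 30 v 30, by share of variance carried by the 10 factors:

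| Features | 30% | 50% | 70% | 90% |
|---|---|---|---|---|
| 300 | 0.998 | 0.97 | 0.87 | 0.73 |
| 1000 | 1.00 | 0.98 | 0.89 | 0.73 |

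Repeat runs agree to within about 0.02. For shares from 0 to 70% the range is therefore about 0.85 to 1.00 at 300 to 1000 features, and about 0.81 to 0.99 at 100 features. A 90% share lowers it to about 0.73, still well above the 0.50 expected by chance.

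**Step 3: importance scores under the null.** With one predictive component, VIP for feature j is √p × |w_j|, where p is the number of features and the squared weights sum to 1. Hence the mean of VIP² is 1. If null weights are roughly normal, the share above 1 is P(|Z| > 1) = 0.32. The simulations give 0.32 to 0.33 at 30 v 30: about 33 of 100, 160 of 500 and 320 of 1000 features.

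**Step 4: adding an uncorrected test.** The features with both VIP > 1 and p < 0.05 number about 5 of 100, 24 of 500 and 49 of 1000. That is the nominal 5%: in these null runs VIP > 1 removes almost nothing that p < 0.05 admits. All are false.

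**Step 5: adding error control.** With Benjamini-Hochberg at 5% on the same null data, any metabolite at all is listed in about 2 to 7% of runs at 30 v 30, and in at most about 10% across all settings run. With 100 runs the Monte Carlo standard error around 5% is √(0.05 × 0.95 / 100) = 0.022, so the 30 v 30 results are in line with the nominal level.

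**The case against.** The strongest reply is that the article gives the analysis only two sentences. Importance cut-offs, validation and multiplicity rules commonly sit in an analysis plan or full protocol, neither of which is shown. That stands in part. A reader might infer that the trial has no false-positive control; the article supports only that it states none.

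It is also fair that the simulated selection rule is assumed. VIP appears nowhere in the article, nor does the number or correlation of features. A reader might go on to say that separation will be near perfect, that the trial will report key substances whatever the truth, or that a third of features are flagged whatever the data. None of this follows. Near-perfect separation needs hundreds of features that are not too strongly correlated. What is reported depends on the unstated rule. The one-third share is a null result: with real signal in 300 features, VIP > 1 flagged 12%, 16% or 56%, depending on how many features were shifted and by how much. PCA cannot force separation, because it does not use the labels.

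Nor does this conflict with section 2.2, which sizes the study "rather than to satisfy hypothesis testing". A screen for candidates in an exploratory pilot is consistent with a sample not sized for a test, and the exploratory aim does soften the case for strict error control.

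What the reply does not remove is this: even an exploratory screen needs a rule for what counts as a hit when the hits are the primary outcome, and the one group-comparing method named does not supply one.

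**Conclusion.** The point holds as a recommendation (should change) with a limited claim. The primary outcome is a data-selected list, OPLS-DA is the only supervised method named for producing it, and neither in-sample separation nor importance from that model is evidence of a difference at this sample size.

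How well noise is separated rests on the assumed feature count and correlation. The counts of falsely flagged features rest on the assumed VIP cut-off, under which the proportions barely change with either. The conclusion about in-sample fit holds across every setting tried, because fitted accuracy was well above chance while the groups did not differ. If the unseen analysis plan already specifies validation and a false discovery limit, what remains is to state them with the outcome definition.

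**What to change.** - **Section 2.9:** define the primary outcome as the metabolites that pass a Benjamini-Hochberg false discovery rate of 5% in a per-metabolite comparison of KOA patients with volunteers on log intensity. Name the baseline sample, because sections 2.5 and 2.6 have patients sampled before and after treatment.
- **Section 2.7:** keep PCA and OPLS-DA as descriptive displays. Report OPLS-DA only with its cross-validated Q2 and a label-permutation p-value.
- **Section 2.7:** send only the passing metabolites to KEGG, and report an empty list as such if none pass.

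Cost: some wording and a little more analysis work, with no new participants, samples or assays. The downside is a shorter list of candidates; features that miss the limit can still be shown, labelled as unconfirmed.
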